### Data analysis

The primary analysis of the primary outcome is a regression model with the stratification variables (gender/LHB area), age group (16-44, 45-59, 60+) and baseline activity level (GPPAQ) included as covariates. In the event that the primary outcome has a highly skewed or bimodal distribution, it will be recoded as a five level ordinal variable, and ordinal regression used in the primary and secondary analyses. These analyses will be conducted on an intention-to-treat basis, in which each participant is coded according to the treatment condition to which they were randomised. A secondary analysis of the primary outcome repeats the primary analysis, but excluding baseline activity level as a covariate. For the primary outcome only, the primary and secondary analyses will be conducted (i) for all participants completing the 7-DAY PAR and (ii) with the addition of multiply imputed values of the primary outcome for those who did not complete the 7-DAY PAR but who did complete either the Baecke or GPPAQ instruments at 12-month follow-up.

The primary analysis for the primary outcome, and for imputed values of 7-DAY PAR, is repeated to conduct sub-group analyses for each of the following variables: gender, age group (16-44, 45-59, 60+), referral reason (mental health only, CHD only, or combination of CHD and mental health), Welsh Index of Multiple Deprivation tertile, fidelity of programme implementation in LHB area (high/low). In each case, the statistical significance of sub-group effects is assessed by including an interaction term in separate models for each respective sub-group variable, with each model also including the main effect for the respective sub-group variable. An analysis to identify whether outcomes vary in terms of exposure to the programme replaces the binary intervention group variable with the three level programme attendance variable.

The analyses described in the preceding two paragraphs are also conducted for the secondary outcome. However, the primary analysis for the secondary outcome (HADS anxiety and depression scales) is conducted only among participants referred for mental health only or a combination of mental health and CHD reasons. The analyses of the secondary outcome among all participants is secondary to this analysis.

Other analyses to be conducted, but not associated with formal hypothesis testing, will include an analysis of baseline demographic characteristics and their relationship with outcomes and the relationship between 6-month intermediate variables and the primary and secondary outcomes. This analysis will require complex multivariable models and mediation analyses estimated within a multilevel modelling framework to allow for independence in measures within individuals (over time) and within exercise specialist.

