• Initial face to face consultation with EP on entry - lifestyle questionnaire, health check (resting heart rate, blood pressure, BMI, and waist circumference), introduction to facilities, MI and goal setting

• Access to one to one exercise instruction and/or group exercise classes

• Discounted rate for exercise activities £1 per session.

• Four week telephone consultation with EP - review of goals and MI

• Sixteen week face to face consultation with EP - review of goals, MI, health check, lifestyle questionnaire, service evaluation questionnaire [23] and signposted to exit routes

Post 16 week activities

• Range and cost of exit routes dependent on area

• 8 months contact by phone to check progress

• 12 months face to face review including Chester fitness step test [24].

Consultations occur at entry, 4 weeks (by phone) and 16 weeks. Following this, participants are contacted by telephone at 8 months to monitor progress and at 12 months they are invited to attend a review session. Routine programme monitoring systems are maintained by EPs and capture the dates of and records from initial, 4 and 16 week and 8 and 12 month consultations.

The Welsh Assembly Government commissioned an independent evaluation of the scheme as it was implemented in 13 of the 22 LHBs in Wales during phase one. This evaluation was to focus on the effectiveness of the scheme among two priority patient groups, those referred for mental health reasons (anxiety and depression) or for CHD risk factors This paper reports upon the design of the national evaluation, which utilised a randomised controlled trial design with nested process and economic evaluations, and reflects on issues in the development and implementation of the evaluation design for current challenges in policy evaluation [25,26]. Ethical approval for the study was obtained from the Thames Valley Multi-centre Research Ethics Committee (Ref: 06/MRE12/85). Approval from medical directors within each LHB was also obtained.

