### Sample size

The trial sample size was determined to detect a difference in the primary outcome, total minutes of weekly exercise at 12 months. The planned sample size of 1052 participants in each group, has 90% power to detect an effect size of 0.15 with no loss to follow-up, and, more realistically, 84% and 87% power to detect an effect size of 0.15 if 25% and 20% respectively of randomised participants are lost to follow up.

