### Nested process evaluation

A nested process evaluation examined programme theory, programme implementation and how NERS was received, facilitating an in-depth understanding of the views of providers and users, as well as interpretation of outcome effects [51]. Guided by the framework proposed by Steckler and Linnan [52], the process evaluation explored diffusion of the national policy across local contexts, fidelity and dose of implementation, patient experiences, programme reach and recruitment. The process evaluation adopted a pluralistic multi method approach involving triangulation [53] of multiple perspectives and methods (Table 2). All analysis will be conducted prior to any knowledge of outcome effects to guard against interpretation bias

**Table 2 T2:** Process evaluation methods

Participants	Methods	Areas for investigation
Welsh Assembly Government representatives (n = 3)	Group interviews and email/telephone communication	Programme theory Programme diffusion and barriers and facilitators to implementation

General Practices (n = 9)	Group interviews with primary care clinicians (GPs, practice nurses; practice managers)	Recruitment Uptake and reach

All exercise co-ordinators (n = 12)	One to one telephone interviews	Fidelity and dose Programme diffusion and barriers and facilitators to implementation Recruitment Uptake and reach Trial experience and implementation

All exercise professionals (n = 38)	One to one telephone interviews	Fidelity and dose Patient experiences - perceived impact and processes of change Uptake and reach Trial experience and implementation

Patient interviews (n = 32 within 6 centres)	Group and one to one interviews with patients at varying stages of the scheme	Patient experiences - perceived impact and processes of change

Exercise professionals (n = 23)	Recordings of at least one first consultation for all exercise professional and coding using Behaviour Change Counselling Index (BECCI; (Lane, Huws-Thomas et al. 2005).	Fidelity

Routine monitoring data (1080 patients)	Secondary analyses	Fidelity and dose Uptake and reach

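### The primary regression and the power figures make no allowance for correlation among intervention participants who share an exercise professional; if it is positive, the interval is too narrow and the power optimistic

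*Protocol article*

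**What the plan says.** **Primary model.** The Data analysis section of the protocol article states: "The primary analysis of the primary outcome is a regression model with the stratification variables (gender/LHB area), age group (16-44, 45-59, 60" (the oldest group has no upper limit). Baseline GPPAQ level is a further covariate. If the outcome is highly skewed or bimodal, it is recoded to five ordered levels and analysed by ordinal regression. Neither route has a term for EP or centre.

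**Power.** Sample size section: "The planned sample size of 1052 participants in each group, has 90% power to detect an effect size of 0.15 with no loss to follow-up". Once losses are counted, the section gives "84% and 87% power to detect an effect size of 0.15 if 25% and 20% respectively of randomised participants are lost to follow up". The inputs are the number per arm, the effect size and the loss. There is no ICC and no design effect.

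**Delivery.** The description of the Welsh scheme gives intervention participants motivational consultations with an EP and "Access to one to one exercise instruction and/or group exercise classes". Table 2 of the process evaluation lists "All exercise professionals (n = 38"). Under Randomisation, controls get usual care and a leaflet.

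**Where the dependence is recognised.** The last paragraph of Data analysis describes exploratory models "estimated within a multilevel modelling framework to allow for independence in measures within individuals (over time) and within exercise specialist". The word independence there evidently means non-independence. That paragraph covers analyses that carry no formal hypothesis test.

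**The concern.** Participants are randomised individually, but those in one arm are then treated by a limited number of EPs. If EPs differ in effectiveness, outcomes within a caseload are correlated in the intervention arm and not in the control arm: a partially nested design.

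The article expects delivery to vary. It calculates fidelity by area and exercise professional, rates recorded consultations for motivational interviewing, and tests whether effects differ between high- and low-fidelity areas. It models the resulting correlation where nothing is tested and leaves it out of the primary analysis.

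LHB as a covariate removes area differences common to both arms. It does not absorb differences between EPs in the same area that act on treated participants only. At stake are the width of the primary confidence interval, the error rate of the primary test and the credibility of the 84% and 87% power figures.

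**Working it through.** **Inputs from the article:** 1,052 per arm; standardised effect 0.15; loss of 20% or 25%; 38 EPs; clustering in the intervention arm only.

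**Assumptions:** two-sided 5% test (not stated, but it reproduces the figures below); equal caseloads; total variance 1 in each arm; ICC from 0.005 to 0.05, because the article gives none.

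**Step 1: reproduce the stated power under independence.** Power = Φ(0.15·√(n/2) − 1.96).
- 20% loss: n = 1,052 × 0.80 = 841.6. The result is 86.8% (stated 87%).
- 25% loss: n = 1,052 × 0.75 = 789. The result is 84.6% (stated 84%).

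Both agree within a point, so these figures contain no allowance for clustering. The no-loss figure computes to 93.1% against the stated 90%. That is a separate mismatch and is not evidence on this point.

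**Step 2: inflate the treated arm only.**
- Caseload: m = n/38, which is 841.6/38 = 22.1 at 20% loss and 789/38 = 20.8 at 25% loss.
- Treated-arm design effect: DE = 1 + (m − 1)·ICC.
- Standard error: SE = √((DE + 1)/n).
- Power = Φ(0.15/SE − 1.96).
- Ratio of true to naive SE: r = √((1 + DE)/2).
- Type I error if clustering is ignored: 2·(1 − Φ(1.96/r)).

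Example, 20% loss and ICC 0.01: DE = 1 + 21.15 × 0.01 = 1.211; SE = √(2.211/841.6) = 0.0513; power = Φ(2.926 − 1.96) = 83.3%; r = √(2.211/2) = 1.052; type I error 6.2%.

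| ICC (assumed) | DE, 20% loss | SE ratio, 20% loss | Power, 20% loss (stated 87%) | Naive type I error, 20% loss | Power, 25% loss (stated 84%) |
|---|---|---|---|---|---|
| 0.005 | 1.106 | 1.026 | 85% | 5.6% | 83% |
| 0.01 | 1.211 | 1.052 | 83% | 6.2% | 81% |
| 0.03 | 1.634 | 1.148 | 76% | 8.8% | 74% |
| 0.05 | 2.057 | 1.236 | 70% | 11.3% | 68% |

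Unequal caseloads make this worse. Replacing m by (1 + CV²)·m with an assumed CV of 0.6 gives, at 20% loss, 82% at ICC 0.01 and 65% at ICC 0.05.

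**Step 3: covariate gain.** The stated power is that of an unadjusted comparison, but the primary model adjusts for GPPAQ, age group, gender and LHB. If these explain a share R² of the variance, SE is multiplied by √(1 − R²), with the ICC read as that of the residuals. With an assumed R² of 0.10 and ICC 0.01:
- 20% loss: SE = 0.0513 × 0.949 = 0.0486, power 87.0%.
- 25% loss: power 85.0%.

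The same R² at 20% loss gives SE = 0.0559 × 0.949 = 0.0531 and 81% at ICC 0.03, and SE = 0.0603 × 0.949 = 0.0572 and 75% at ICC 0.05. The offset is complete at small ICC and only partial at larger values. It bears on power and does not correct the naive type I error.

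**The case against.** **The error-rate claim is conditional.** Randomisation is individual and stratified by LHB. If the scheme affects nobody, EPs create no correlation in the treated arm, and catchment differences fall on both arms alike. The inflated error rates need EP effects that vary in the treated arm, average zero, and belong to EPs regarded as a sample from a wider population. Table 2 speaks of all EPs, so one may treat them as fixed and confine inference to the scheme as these people delivered it. The conditionality stands. The fixed reading does not dispose of the point: the Discussion claims high reproducibility and external validity for a national scheme, and phase one covered 13 of 22 LHBs.

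**The ICC may be small.** The outcome is measured at 12 months, well after a 16-week programme, by interviewers blind to allocation, and analysed by intention to treat, so it includes people who never attended. This is fair. At ICC 0.005 the power loss is under 2 points.

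**One EP per participant is not stated.** The 38 comes from a process-evaluation table, not a caseload record. That also stands, so the caseload of about 22 is an approximation.

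**An analysis plan could settle the variance estimator.** It could. However, the article names the primary model's terms and places the EP level expressly in the exploratory work, so this is more than an unstated detail.

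**A stronger reading to avoid.** A reader might infer that type I error definitely exceeds 5%, or that 84% and 87% power are unreachable unless the ICC is exactly zero. The documents support neither: no ICC is given, and a modest covariate gain restores 87% at ICC 0.01 and 20% loss.

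**Conclusion.** The point holds in conditional form. The primary regression and the power figures leave out correlation within EP in the intervention arm, which the article itself recognises elsewhere, and LHB adjustment does not supply it. If the correlation is positive and inference is meant to extend beyond these EPs, the error runs in the anti-conservative direction. Its size depends on an ICC that the documents do not give: minor at 0.005, moderate at 0.01, and serious at 0.03 to 0.05, where covariate adjustment at an assumed R² of 0.10 no longer restores the stated power at 20% loss. These results rest on 38 equal caseloads, one EP per participant and a two-sided 5% test.

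**What to change.** Settle the following before the outcome analysis; randomisation and sample size are unaffected.

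1. Make the primary model partially nested, with a random EP effect in the intervention arm only and small-sample degrees of freedom, or use EP-clustered variance. Specify the equivalent for the ordinal route.
2. Fix a rule for intervention participants who never attended: assign them to their referral centre or treat each as a singleton.
3. Report power over a stated ICC range that includes 0.005, as conditional figures, and say whether covariate gain is counted.

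**Cost.** The interval widens: negligibly if the ICC is near zero, and by up to about 24% at ICC 0.05 with 20% loss (SE ratio 1.236). Participants must also be linked to EPs through the programme monitoring data, which the article already uses for fidelity by exercise professional and for attendance.

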##### - Programme implementation fidelity

Scores for fidelity to protocols are calculated for each of the 12 areas by allocating a score of 1 each time for; an instance of 4 week contact being made with patients who have stopped attending at this point, for follow up consultations being conducted at 8 months, and for consultations at 12 months with those completing the programme. A score of 0 was allocated for each instance of non contact, providing a range of 0 to 3 and allowing calculation of percentage fidelity overall and by area/exercise professional. An additional measure of fidelity is the quality of goal setting, with goal records coded as measurable and time bound (1) or as not measurable and time bound (0), allowing calculation of percentage fidelity overall and by area/exercise professional.

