### Recruitment

Trial recruitment occurred in 12 of the 13 areas, with one area failing to start a scheme during the trial period. Between July 2007 and October 2008, 4,779 health professional referrals were received by the evaluation team. Of these, 1,493 were not eligible for the trial and their referral forms were forwarded to the ECs for processing directly onto the scheme. The remaining 3,286 were sent full informed consent information and a baseline questionnaire. In total 2,160 patients were recruited to the trial, with 890 not responding and 236 not consenting to participate in the trial.

Respondents ranged between 16 and 88 years old, with a mean age of 52 (SD 14.7) and the vast majority classed themselves as white (96%). Whilst, measures of area deprivation ranged from 2.3 to 81.0 with a mean of 22.6 (SD 14.6). Table 3 shows that the majority were referred for CHD risk factors on their own (72%) or in combination with mental health conditions (24%), with only 4% referred solely for mental health reasons. Those recruited were most likely to be female (66%), to be married or with a partner (61%) and there was a fairly equal split between those employed (31%) and retired (32%). Finally, whilst the majority referred onto the scheme classified themselves as either inactive or moderately inactive (74%), 24% defined themselves as either active or moderately active.

**Table 3 T3:** Baseline measures for recruited sample

Measure	% (N)
**Reasons for referral** CHD CHD and Mental Health Mental Health	72.2 (1,559) 24.2 (522) 3.7 (79)

**Gender** Female Male	65.5 (1,415) 34.5 (745)
**GPPAQ** Inactive Moderately inactive Moderately active Active Missing	58.6 (1,266) 15.3 (330) 15.8 (342) 8.2 (176) 2.1 (46)
**Employment** Retired Employed Housework Other Seeking work Student Missing	31.9 (666) 30.8 (646) 19.1 (413) 13.1 (282) 3.2 (69) 1.9 (40) 2.0 (34)
**Education** > Minimum education	52.1 (1,127)
**Marital status** Married/Partner Single Divorced/Separated Widowed Missing	61.4 (1,326) 17.8 (384) 13.6 (293) 6.0 (129) 1.3 (28)

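### The fidelity subgroup varies only between 12 areas but is tested at participant level, with no allowance for treatment effects that differ between areas for other reasons

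*Protocol article*

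**What the plan says.** All references are to the protocol article.

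- **Primary model (Data analysis).** A "regression model with the stratification variables (gender/LHB area), age group (16-44, 45-59, 60+) and baseline activity level (GPPAQ) included as covariates". LHB area is therefore already in the model. The text does not say whether it is fixed or random, and listing it as a covariate reads as fixed.
- **Subgroups (Data analysis).** That model is repeated for five variables, one of them "fidelity of programme implementation in LHB area (high/low". For every one, "the statistical significance of sub-group effects is assessed by including an interaction term in separate models", "with each model also including the main effect for the respective sub-group variable".
- **Multilevel models (Data analysis, last paragraph).** These are named only under "Other analyses to be conducted, but not associated with formal hypothesis testing", and there for clustering within individuals over time and within exercise specialist. LHB is not mentioned.
- **Number of areas (second Recruitment section).** "Trial recruitment occurred in 12 of the 13 areas".
- **Fidelity score (Programme implementation fidelity).** Scores are calculated by area from three 0/1 items: "an instance of 4 week contact being made with patients who have stopped attending at this point", the 8-month follow-up, and the 12-month consultation with completers. "A score of 0 was allocated for each instance of non contact, providing a range of 0 to 3". Quality of goal setting is a further measure.

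**The concern.** Gender and age group vary between participants within every area, so a participant-level interaction has ample replication. Fidelity does not vary within an area. Every participant in an LHB carries the same label, and the comparison is the average treatment effect in high-fidelity areas against that in low-fidelity areas. Areas may also differ in effect because of facilities, local population or exit routes, and the scheme description says that the range and cost of exit routes depend on area. That variation belongs in the standard error of the fidelity contrast, but the interaction as described uses only participant-level residual variation.

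At stake is a policy message. The Discussion says that monitoring data will be used to assess how adherence and fidelity affect effectiveness. A chance imbalance between two sets of areas could be reported as evidence that the scheme works where it is delivered faithfully.

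**Working it through.** **Inputs from the article.** 12 areas; planned sample 2 × 1,052 = 2,104; loss scenarios of 20% and 25%; design effect size 0.15. The article gives no between-area SD of the treatment effect and no type I error figure for this test, so there is no stated figure to reproduce.

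**Assumptions.** Equal area sizes, 1:1 allocation within area, outcome SD 1, two-sided 5%, and tau (between-LHB SD of the treatment effect, after fidelity) from 0 to 0.20 outcome SD.

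**Step 1: participants per area.** 2,104 × 0.8 / 12 = 140.3.

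**Step 2: sampling variance of one area's effect.** 4 / 140.3 = 0.0285.

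**Step 3: variance inflation.** The true variance of an area effect is 0.0285 + tau², while the planned test uses 0.0285. Inflation = 1 + tau² / 0.0285. With equal area sizes the high/low split cancels from this ratio.

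**Step 4: type I error** = 2 × (1 − Φ(1.96 / √inflation)).

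| tau (assumed) | Inflation | 1.96 / √inflation | Type I error |
|---|---|---|---|
| 0 | 1.00 | 1.96 | 5.0% |
| 0.05 | 1.09 | 1.88 | 6.0% |
| 0.10 | 1.35 | 1.69 | 9.2% |
| 0.15 | 1.79 | 1.47 | 14.3% |
| 0.20 | 2.40 | 1.26 | 20.6% |

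**Step 5: check by simulation.** 2,000 runs per setting, with 6 high and 6 low areas. The sizes were 66 per arm per area (about 25% loss: 1,052 × 0.75 / 12 = 65.75) and 88 (no loss: 1,052 / 12 = 87.7).

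| tau | 66 per arm: formula / simulated | 88 per arm: formula / simulated |
|---|---|---|
| 0 | 5.0% / 5.1% | 5.0% / 4.8% |
| 0.05 | 6.0% / 5.5% | 6.3% / 6.1% |
| 0.10 | 8.9% / 8.3% | 10.2% / 11.4% |
| 0.15 | 13.8% / 14.0% | 16.5% / 16.3% |
| 0.20 | 19.8% / 17.9% | 23.8% / 24.1% |

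A t-test on the 12 area effects (10 degrees of freedom) rejected in 4.8% to 5.8% of runs across all these settings.

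**Step 6: the prescribed main effect.** Twelve LHB indicators, arm, fidelity and arm by fidelity make 15 columns of rank 14. Without the fidelity main effect there are 14 columns of rank 14. With fixed LHB effects the main effect is therefore redundant, and the interaction is estimable either way.

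**Step 7: the fidelity score.** If each patient were scored out of 3, and nobody who stopped came back, someone who had stopped by week 4 could earn the 4-week and 8-month points (2). A completer could earn the 8-month and 12-month points (2). Someone stopping between weeks 4 and 16 could earn only the 8-month point (1). At area level, different patients supply different items, so 3 can be reached.

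**The case against.** **The inflation is conditional.** A reader might infer that the test is anti-conservative outright. The article does not support that. With tau = 0, or with these 12 areas taken as the whole population of interest, the test keeps 5%. Tau is nowhere given, and the larger figures need a between-area SD equal to or above 0.15, the whole effect the trial is powered for. At tau of 0.05 to 0.10 the error is 6% to 9%. This objection stands and sets the size of the point. It does not remove it: phase one covered 13 of 22 LHBs, and the Discussion claims high external validity and minimal control over implementation. Inference limited to these areas, with a uniform effect apart from fidelity, fits that poorly.

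**The main effect does no harm.** A reader might infer that the rank deficiency breaks the analysis. It does not. LHB absorbs the main effect and the tested interaction is unchanged. With a random LHB intercept, which the text does not state, the main effect would be estimable.

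**The score's maximum.** A reader might infer that the stated maximum of 3 is impossible. That holds only if each patient is scored, whereas the section says that scores are calculated for each area. Contacts made over contacts due is a natural reading of the existing text. What remains is that the wording allows more than one unit and denominator.

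**Limited reach.** This is one of five subgroup analyses and leaves the primary estimate untouched. The process evaluation, which covers fidelity, is to be analysed before outcome effects are known, which guards against tuning the labels. It does not guard against chance differences between areas.

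**Conclusion.** The point holds in conditional form. Fidelity is a moderator with 12 units, and the article specifies a significance test that leaves out between-area variation in the treatment effect. If that variation is present and the conclusion is meant to carry beyond these areas, the nominal 5% becomes about 6%, 9%, 14% or 21% at tau of 0.05, 0.10, 0.15 or 0.20. These figures rest on equal area sizes, about 140 analysed per LHB and an assumed tau. The multilevel framework in the article covers other analyses and other levels, so it does not meet the point. The redundant main effect and the loosely worded score are minor matters of specification. This is a worthwhile, inexpensive correction to one subgroup analysis and no threat to the trial's main result.

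**What to change.** **Main change.** For the fidelity subgroup only, replace the ordinary interaction test by one of the following:

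- a model with a random treatment slope by LHB, testing arm by fidelity with small-sample degrees of freedom; or
- a regression of the 12 area-specific treatment effects on fidelity (high/low or the percentage), using t on 12 − 2 = 10 degrees of freedom.

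Apply the same to the repeats of this subgroup analysis on the imputed primary outcome and on the anxiety and depression scales.

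**Asides.** State that the fidelity main effect is dropped where LHB enters as fixed effects. Define percentage fidelity as contacts made divided by contacts due, counting each item only for patients for whom it was due. The high/low label then cannot partly reflect dropout pattern, as it would if patients were scored out of 3.

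**Cost.** Analysis wording, and a clear definition of a variable computed from monitoring data already held. The price is a wider interval. With 66 per arm per area and a 6/6 split, the standard error of the interaction is √((2/66 + tau²) × (1/6 + 1/6)): 0.1005 at tau = 0 and 0.1159 at tau = 0.10. With the t multiplier of 2.228 in place of 1.960, the half-width goes from 1.960 × 0.1005 = 0.197 to 2.228 × 0.1005 = 0.224 at tau = 0, or to 2.228 × 0.1159 = 0.258 at tau = 0.10. Little real power is given up: even at tau = 0 the participant-level test has only about 32% power for an interaction of 0.15.

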##### - Anxiety and depression

The Hospital Anxiety and Depression Scale (HADS) [36] was used to assess depression and anxiety at 12 months. Scores on each of the two scales can range from 0-21, with higher scores indicating greater levels of anxiety or depression. HADS has been used extensively and has performed well in a variety of populations: A review of 747 studies concluded that it performed well in assessing the severity and presence of anxiety disorders and depression in both somatic and psychiatric cases in primary care patients and the general population [37].

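### The main all-participant HADS model has no term for referral reason, the only baseline mental health indicator described, and so gives up some precision

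*Protocol article*

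**What the plan says.** In the Data analysis section of the protocol article, the primary model for weekly activity is "a regression model with the stratification variables (gender/LHB area), age group (16-44, 45-59, 60+) and baseline activity level (GPPAQ) included as covariates". A secondary version drops GPPAQ. The section carries these models to HADS: "The analyses described in the preceding two paragraphs are also conducted for the secondary outcome".

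The population for HADS is then narrowed: "the primary analysis for the secondary outcome (HADS anxiety and depression scales) is conducted only among participants referred for mental health only", or for mental health combined with CHD. The wider analysis is kept with lower status: "The analyses of the secondary outcome among all participants is secondary to this analysis".

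Referral reason, in three levels, is one of the sub-group variables. Each sub-group model contains the main effect of its variable and the interaction with arm. It is not in the covariate list of the main model.

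On measurement, the section on anxiety and depression says that HADS "was used to assess depression and anxiety at 12 months". EQ-5D and SF-12 are described at 6 and 12 months. The section on pre-randomisation baseline measures lists demographics, willingness to pay, GP visits and GPPAQ, but no mental health scale. Randomisation is stratified by gender and LHB only. Table 3 gives referral reason for all 2,160 recruited: 1,559 CHD, 522 CHD and mental health, 79 mental health.

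**The concern.** GPPAQ gives the activity model a baseline measure of the construct that the primary outcome measures. HADS inherits the same covariate set, in which nothing describes mental health at entry. Referral reason is the one baseline variable described that does so, and the plan treats it as relevant to HADS by restricting the primary HADS analysis on it.

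The all-participant HADS analysis removes that restriction and puts nothing in its place. It mixes people referred for anxiety, depression or stress with people referred for CHD risk only. If the two groups differ in HADS at 12 months, the difference stays in the residual variance. Stratification does not balance referral reason between arms either. What is at stake is the width of the confidence interval for the all-participant HADS effect.

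**Working it through.** **The plan's own figure.** The article gives no power or precision figure for HADS, so there is none to reproduce.

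**Inputs.** From Table 3: mental-health referrals, alone or with CHD, 79 + 522 = 601; CHD only 1,559; total 2,160. Hence p = 601/2,160 = 0.278 and p(1−p) = 0.201. The gap d in 12-month HADS between the two groups, in within-group SDs, is not in the article. It is assumed, over the range 0.3 to 1.0.

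**Variance explained in the all-participant analysis.** With referral reason as two groups (any mental health v CHD only):

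- R² = p(1−p)d² / (1 + p(1−p)d²)
- ratio of standard errors, with v without the term = √(1−R²)
- equivalent gain in sample size = 1/(1−R²) − 1

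| Assumed d | R² | SE smaller by | Equivalent gain in n |
|---|---|---|---|
| 0.3 | 1.8% | 0.9% | 1.8% |
| 0.5 | 4.8% | 2.4% | 5.0% |
| 0.75 | 10.1% | 5.2% | 11.3% |
| 1.0 | 16.7% | 8.7% | 20.1% |

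Example at d = 0.5: 0.201 × 0.25 = 0.0502; 0.0502/1.0502 = 0.048; √0.952 = 0.976.

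These are marginal figures. Any part of the gap already explained by gender, LHB, age group or GPPAQ would reduce them.

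**In terms of power.** Assume a standardised HADS effect of 0.15, two-sided 5% and 810 per arm (2,160 less 25%, split equally). Power is 85.5% without the term, 86.1% with it at d = 0.3, and 91.1% at d = 1.0.

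**The restricted primary HADS analysis.** Here only mental health alone (79) v combined (522) remains: q = 79/601 = 0.131 and q(1−q) = 0.114. An assumed gap of 0.25 gives R² = 0.7%; a gap of 0.5 gives 2.8%. The equivalent gain in sample size is about 1% to 3%.

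**Does the omission bias the effect?** With complete data, no, because arm is randomised. With incomplete HADS data, bias through this route needs the retained share of mental-health referrals to differ between arms. Three illustrations, with all retention rates assumed:

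- Retention 70% for mental-health and 75% for CHD-only referrals in both arms: the retained share is 0.278×0.70/(0.278×0.70 + 0.722×0.75) = 0.265 in each arm, so the bias is zero.
- Retention 75% everywhere except 65% among mental-health controls: shares 0.278 v 0.250, a difference of 0.028, hence a bias of 0.014 SD at d = 0.5 and 0.028 SD at d = 1.0.
- The same with 55%: shares 0.278 v 0.220, hence 0.029 SD at d = 0.5 and 0.058 SD at d = 1.0.

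**The case against.** The strongest reply is that nothing here is an error. Adjusting for the stratification factors, age group and baseline activity is a valid pre-specified model, and it agrees with how randomisation was done. The plan also uses referral reason for HADS twice: by restricting the primary analysis, and by including its main effect in the referral-reason sub-group model. What remains is one model for a secondary outcome that is labelled secondary, with a gain that depends on an unstated gap. Table 1 sets the mental health criterion at mild symptoms, so a gap as large as 1.0 SD cannot be taken from the article. At 0.3 SD the gain is trivial.

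Most of this stands. It limits the point to the main all-participant model and keeps its weight low. Two parts do not remove it. The sub-group model is there to test whether the effect varies; the overall all-participant effect comes from the model without the term. Nor is this a detail left open for the analysis plan: the article states the covariate set and applies it to HADS.

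A reader might infer two stronger claims:

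- **That every HADS analysis ignores referral reason.** The restriction and the sub-group model show otherwise.
- **That a known predictor of missing HADS data is left out, so the complete-case result is biased.** The article limits multiple imputation to the primary outcome, but nowhere links referral reason to non-response. Such a link is plausible at most, and through this route it would matter only if it differed by arm.

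**Conclusion.** The point holds for the main all-participant HADS model, as a matter of precision only. That model pools 601 mental-health referrals with 1,559 CHD-only referrals and has no covariate that describes mental health at entry.

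The standard error is larger than it need be by an amount that rests wholly on the assumed 12-month gap: adding the term would reduce it by about 1% at 0.3 SD and about 9% at 1.0 SD, less whatever the other covariates already capture. The randomised comparison is not biased by the omission, and the article does not support a missing-data argument.

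The primary HADS analysis is barely affected. Because the affected analysis is explicitly secondary, the weight is minor. This is a free improvement, not the correction of an error.

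**What to change.** State that the all-participant HADS analyses, with and without GPPAQ, include referral reason as a three-level covariate (CHD only, combined, mental health only) alongside the existing ones. Fix this in writing before HADS outcomes are analysed.

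In the restricted primary HADS analysis, a term for mental health only v combined is optional, given the small gain.

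The cost is one line of wording and two degrees of freedom. No new data are needed, and no participant is lost, since Table 3 classifies all 2,160 by referral reason.
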